## **Investigation tools validity and reliability**

### **4.11.3. Validity of data**

Questionnaire -Questions have been adopted from standardized instruments which have been tested within the Sub-Saharan region

WHO Global school-based student health survey (WHO, 2013)

- i. C-OIDP-measures of oral health quality of life (Slade, G.D., 1997),
- ii. Socio-economic status - international wealth index (Smits and Steendijk, 2015)

Oral clinical examination will be done using standardized measures

- i. Dental plaque Index - Sillness and Loe index (Löe, 1967)
- ii. Gingival bleeding - Sillness and Loe index (Löe, 1967)
- iii. Dental caries status - Caries Assessment Spectrum and Treatment (CAST) (Frencken *et al.*, 2011)

### **4.11.4. Reliability of data**

Training and Calibration of examiners

The principal investigator (SA) is a specialist in restorative dentistry with adequate skills in dental caries diagnosis. In respect to use of Caries Assessment Spectrum and Treatment (CAST) in caries assessment the one of the inventors of the tool has provided the CAST manual and provide blended training followed by calibration. The PI will later train the two examiners (dental surgeons) on dental plaque index, gingival bleeding index and CAST for a total duration of 2 days. Training will include the rationale of using the indices their codes and description, ergonomic guidelines and instructions on how to perform examination. Pictures of clinical situations related to each code of each index will be shown. For CAST index examples of each code will be shown on extracted teeth first. The trainees will be given a number of examination exercise and their results compared to expert. Any differences will be discussed and examination repeated and in so doing the trainee will understand the tool. Training on plaque index and bleeding index will be done on adolescents with similar age group 10-14 years

Examination of 5-10 subjects aged 10-14 pre selected adolescents with full range of CAST codes will be done by each examiner and the PI then results compared. The differences will be discussed and then examination repeated. When agreement is obtained

a new set of 5-10 adolescents will be examined by trainee and results compared. Calibration will be considered sufficient when the examiners and the PI's agreement are at least 85%.

#### **Intra-examiner consistency**

The examiners will be subjected to periodic evaluation for their consistency in the clinical assessment of the indices. Every 10th participant will be subjected to a clinical examination after two weeks to test for reliability of the examiners. The coefficient of reliability will be reported as Cronbach alpha.

#### **4.12. Data entry cleaning and analysis**

Data entry, coding and processing will be done using a computer software program IBM SPSS for Windows (Version 23). Frequency distribution for proportions, means (SD), cross tabulation with chi –square and binary logistic regression reported in odds ratio and 95% (CI) will be performed per respective objectives.

Frequency distribution for proportions of adolescents with plaque, gingival bleeding, poor oral health behaviors and oral health related quality of life. Dental caries experience will be summarized as number and percentage. Furthermore, cross tabulation for bivariate comparison of differences in intervention outcome variables by socio-demographics, study arms and oral health behaviors will be conducted. To examine for the differences between the groups (effectiveness of trial intervention) generalized estimating equations will be performed and reported in odds ratio and 95% confidence interval. A statistical significance difference shall be assumed when  $p \leq 0.05$ . Analysis plan per objective is summarized in appendix 6.

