## Summary

**Background:** Global trends of diseases show an increase of oral diseases in most low and middle- income countries due to increased availability of sugars, inadequate fluoride products and lack of sustainable preventive strategies. Most oral diseases are behavioral related and behaviors acquired during adolescence are likely to be passed to adulthood. Adolescent's oral health behaviors are shaped by family socioeconomic status and therefore socio gradient in oral diseases may be more reflected in this group. Despite increasing oral diseases and World Health Organization (WHO) recommendations of using BPOC as feasible and cost-effective preventive and curative approach of oral diseases, the strategy has not been implemented in Sub-Saharan Africa region.

**Aim:** To evaluate the effectiveness of applying the modified WHO basic package of oral care (BPOC) in improving oral health-knowledge and behaviors, oral health and related quality of life among adolescents in Copperbelt, Zambia.

**Materials and methods:** A cluster randomized controlled field trial with a total sample size of 1760 grade eight secondary school adolescents will be done in Copperbelt province, Zambia. Adolescents in the trial arm will receive a modified WHO-BPOC and the control will maintain their standard of care, both groups will be re-assessed at follow-ups. Data collection on adolescents' demographics, oral health-related knowledge and behavior, impacts of oral disease on daily performance and parental socio-demographics will be done using a self-administered structured questionnaire. Data on dentition status, plaque, and gingival bleeding will be assessed using CAST, Silness, and Loe (1967) plaque and gingival bleeding indices, respectively. Data entry, cleaning, and analysis will be done using IBM SPSS for windows (version 23), and summarized as frequency distribution and cross-tabulations. Adjusted binary logistic regression and generalized estimating equation will be performed to examine the differences between the groups at baseline and follow up in oral health-related behaviors, plaque, gingival bleeding, OHRQoL and dental caries status for various socio-demographics characteristics. The statistical significance difference shall be assumed when  $p \leq 0.05$ .

**Budget of the study:** A total budget of TSh 34,341,450.00 is required to facilitate proposal writing, ethical clearance, purchase of dental materials and supplies, thesis writing and other logistics.

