Proportion of adolescents with plaque ranges from 3.5-27.2% in Europe and America (Vadiakas et al., 2012, Botero et al., 2015, Giacaman et al., 2018) and 16.1-81.1% in Asia and Africa (Yazdani et al., 2009, Mbawala et al., 2010, Berhane et al., 2014, Sukhabogi et al., 2014, Oyedele et al., 2018, Simangwa et al., 2018). The proportion is significantly higher in older, males, and those from rural and low socioeconomic status in all regions (Mbawala et al., 2010, Vadiakas et al., 2012, Oyedele et al., 2018, Simangwa et al., 2018, Giacaman et al., 2018). Plaque is also reported in Africa and Europe to be more among adolescents from lower than higher fathers or mother's education (Mbawala et al., 2010, Vadiakas et al., 2012, Berhane et al., 2014).

Prevalence of gingivitis among adolescents range from 16.7-72.8% in Europe and America (Vadiakas et al., 2012, Botero et al., 2015, Chrysanthakopoulou et al., 2020), 59-100% in Asia and middle east (Sharva et al., 2014, Sukhabogi et al., 2014) and 26.7-40.9% in Africa (Azodo et al., 2015, Simangwa et al., 2018). Gingivitis affects significantly more adolescents in rural than urban areas, males than females (Vadiakas et al., 2012, Nuaimi et al., 2014, Simangwa et al., 2018), those from low socio-economic status families and parents with low education (Mbawala et al., 2010, Vadiakas et al., 2012, Sharva et al., 2014) in all regions. Information on clinically assessed gingivitis among Zambian adolescents could not be retrieved, however a self reported experience of gingivitis is 19% (Hagberg and Sjodahl 2007).

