#### **4.10. Study outcomes**

The expected primary outcomes are improved oral health (dental caries status and gingivitis) and OHRQoL. The secondary outcomes include improved oral hygiene (plaque score) and oral health knowledge and related behaviors. The effect sizes for improvement in oral health and oral health related quality of life are based on average improvement achieved in similar studies reviewed.

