#### **4.9.2.3. Dental plaque**

Will be evaluated as a sticky colorless or pale yellow to brown biofilm on tooth surface (buccal and lingual) of the index teeth (16, 11, 26, 36, 41, 46) and scored based on to Silness-Löe plaque index as follows:

- 0 = Plaque not visible nor cannot be wiped off with the explorer
- 1 = Plaque not visible but can be wiped off with the explorer
- 2 = Plaque is visible along the gingival no need to probe
- 3 = Thick plaque is visible along gingival margin

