#### Notes

- If the index tooth is missing score the nearest tooth in that sextant
- If there is no tooth in that sextant indicate X
- The overall score is sum of the 12 surfaces scores (maximum of 36)

Adolescents Id No.....

| Part 3: Gingival bleeding scores according to Silness-Löe plaque index |             |    |    |
|------------------------------------------------------------------------|-------------|----|----|
|                                                                        | Index teeth |    |    |
| Surface                                                                | 16          | 11 | 26 |
| Buccal                                                                 |             |    |    |
| Lingual                                                                |             |    |    |
|                                                                        | 46          | 41 | 36 |
| Buccal                                                                 |             |    |    |
| Lingual                                                                |             |    |    |

**Codes** 0= No inflammation (Normal gingival, no discoloration, no bleeding)

1= Mild inflammation (slight color change, mild alteration of gingival surface, no bleeding)

2= Moderate inflammation (erythema, swelling, bleeding on probing or when pressure is applied)

3= Severe inflammation (severe erythema and swelling and tendency towards spontaneous bleeding, some ulceration)

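### Plaque is declared as a 0–36 score, but the arms are compared on a yes/no plaque proportion with no stated cut-off

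*Protocol*

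**What the plan says.** **Declared outcome.** Protocol section 4.10: "The secondary outcomes include improved oral hygiene (plaque score) and oral health knowledge and related behaviors".

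**How the score is built.** Section 4.9.2.3 codes the buccal and lingual surfaces of six index teeth from 0 to 3. Code 1 reads "Plaque not visible but can be wiped off with the explorer". The notes to Part 2 of the clinical form (Appendix 2) state: "The overall score is sum of the 12 surfaces scores (maximum of 36". The key to the same part describes a different index: the buccal, lingual, mesial and distal scores added and divided by 4. The form has rows for buccal and lingual surfaces only.

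**Planned analysis.** Section 4.12 describes the plaque summary as "Frequency distribution for proportions of adolescents with plaque, gingival bleeding, poor oral health behaviors". For effectiveness it says "generalized estimating equations will be performed and reported in odds ratio and 95% confidence interval". The Summary states "Adjusted binary logistic regression and generalized estimating equation will be performed" and names plaque among the outcomes on which the groups are compared. Means with SD appear in 4.12 only in a general list of summaries. No between-arm comparison of mean plaque score is described, and no rule says when a pupil counts as having plaque.

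**The concern.** An odds ratio needs a binary outcome, so the plan replaces the declared score with a dichotomy. Two things follow.

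First, the reported effect would not be the effect on the declared outcome. The literature review (section 3.0) expresses the expected benefit of oral health education as an 8 to 67% improvement in plaque score, which is a statement about amount.

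Second, a dichotomy ignores change on either side of its cut-off. A pupil can improve a good deal and keep the same value. Because the cut-off is not written down, it could also be chosen after the data are seen, and different choices give different answers. Section 4.14 regards 24 months as long enough to observe change in plaque, so this outcome is expected to be informative.

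**Working it through.** **1. The plan's own figure.** The sample size (section 4.4) is based on mean DMFT; nothing is calculated for plaque.

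- 2N = 4(1.96 + 1.03)² × 1.34² / 0.268² = 894.01, stated as 894.
- Design effect = 1 + (80 − 1) × 0.01 = 1.79, and 894 × 1.79 = 1600.26, stated as 1600.
- 1600 × 1.10 = 1760, as stated.

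The figure reproduces. Removing the design effect leaves 894 / 2 = 447 effective pupils per arm.

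**2. Inputs for plaque.** The protocol gives no plaque mean, SD or expected effect. As an assumption, take a shift of 0.2 SD, the ratio that the plan uses for DMFT (0.268 / 1.34 = 0.2). Take two-sided alpha 0.05 and the same design effect for score and proportion.

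**3. Power for the score.** z = 0.2 × √(447/2) − 1.96 = 2.99 − 1.96 = 1.03, so power is about 85%.

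**4. Power for a proportion under the same shift.** Let a fraction p of control pupils lie above the cut-off, with c = Φ⁻¹(p). The intervention fraction is q = Φ(c − 0.2). With m = (p + q)/2:

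z = [(p − q)√447 − 1.96√(2m(1 − m))] / √(p(1 − p) + q(1 − q))

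The efficiency relative to the score is φ(c)² / [p(1 − p)].

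Example, p = 0.811: c = 0.882, q = 0.752, m = 0.782, z = (1.242 − 1.145) / 0.583 = 0.17, power 57%.

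| Control proportion | Intervention proportion | Power | Relative efficiency |
|---|---|---|---|
| 16.1% | 11.7% | 48% | 0.44 |
| 50% | 42.1% | 66% | 0.64 |
| 81.1% | 75.2% | 57% | 0.48 |
| 90% | 86.0% | 45% | 0.34 |
| 95% | 92.6% | 32% | 0.22 |
| 99% | 98.3% | 14% | 0.07 |

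The rows 16.1% and 81.1% are the ends of the range that section 3.0 quotes for Asia and Africa. No cut-off in this model exceeds a relative efficiency of 0.64.

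**5. Sensitivity to the distribution.** A second model gives each of 12 surfaces a code of 0–3 as Binomial(3, π), with π varying between pupils as a beta variable. The mean score is cut by 20%, with 447 effective pupils per arm. Two possible cut-offs are shown: any surface coded 1 or more, and any surface coded 2 or more (visible plaque).

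| Mean score (SD) | Any code ≥1 | Any code ≥2 | Power: score | Power: ≥1 | Power: ≥2 |
|---|---|---|---|---|---|
| 3.6 to 2.9 (5.4) | 57% to 49% | 26% to 21% | 52% | 68% | 43% |
| 7.2 to 5.8 (7.2) | 82% to 74% | 49% to 40% | 84% | 80% | 74% |
| 12.0 to 9.6 (6.7) | 98.8% to 96.8% | 81% to 70% | about 100% | 51% | 97% |
| 18.0 to 14.4 (7.3) | 99.9% to 99.5% | 95% to 89% | about 100% | 18% | 95% |

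The beta precision (a + b) is 3 in the first two rows and 6 in the last two. When plaque is sparse and skewed (row 1), the lowest cut-off does better than the score. With heavy plaque that cut-off loses most of the power, while the visible-plaque cut-off loses little. With a 50% fall in mean score, the score and the lowest cut-off both have at least 95% power in all but one of the 12 scenarios run. The exception is a mean of 18 with the least variation between pupils, where the proportion has 56%.

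**The case against.** **The quoted sentence may be only descriptive.** It speaks of frequency distributions, and 4.12 ties its methods to the objectives. Of the objectives in Appendix 6, only the first, on prevalence, touches periodontal status, and a proportion suits it. Objectives 3 to 5 cover knowledge and behaviours, caries and oral impacts, not plaque. This stands as a limit on importance. It does not remove the mismatch: the Summary names plaque among the between-group comparisons, and 4.12 gives the odds ratio as the only between-arm effect measure.

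**The word score is used loosely.** Section 3.0 speaks of a bleeding score when it reports a proportion with bleeding. That is fair, but for plaque the form gives score a numerical definition.

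**A cut-off may be in an analysis plan not shown.** That is possible, so its absence alone is no fault. The point rests on what 4.12 does state: a proportion and an odds ratio for an outcome declared as a score.

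**A stronger reading.** A reader might infer that one surface with code 1 makes a pupil plaque-positive, so that nearly every pupil in both arms is positive and the analysis is blind to large improvements. The documents do not say this. No rule is stated, and section 3.0 quotes proportions with plaque of "16.1-81.1% in Asia and Africa", well short of saturation. Severe loss is one possible consequence of an open cut-off, not a feature of the plan.

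**Conclusion.** The mismatch between declared and analysed plaque outcome is in the text and holds whatever the plaque distribution. Its cost in power is conditional. Under a 0.2 SD shift, power falls from about 85% to 66% at best, to 57% at the upper end of the quoted regional range, and to 32% at 95% prevalence. The size of the shift, the normal latent scale and the common design effect are assumptions. Under a skewed alternative with little plaque, the loss vanishes or reverses, so a general statement that power is lost would go too far.

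A reader might also infer that the trial's conclusions are at risk. They are not: plaque is secondary, the trial is sized on DMFT, and no effect objective in Appendix 6 concerns plaque. The point matters for the correct reporting of one secondary outcome and for closing off a late choice of cut-off.

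**What to change.** In section 4.12, and correspondingly in the Summary, state that the arms are compared on the plaque score by GEE with an identity link and robust errors at school level, adjusted for the baseline score, and reported as a mean difference with 95% CI. Keep any proportion with plaque as descriptive, with its cut-off written down in advance.

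In Appendix 2, Part 2, reconcile the key (four surfaces divided by 4) with the notes (sum of 12 surfaces), so that the score has one definition. The form records buccal and lingual surfaces only, which fits the sum. The definition should also say how the total is formed when a sextant is marked X, for example as a mean per scored surface.

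The cost is wording: the 12 surfaces are already recorded at baseline and follow-up, and no extra data are needed. The one downside is that plaque would be reported on a different effect scale from the outcomes given as odds ratios.

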#### 4.4. Sample size

A sample size of 1760 adolescents calculated using a Cluster Randomized Controlled Trial formula (RCT) and adjustment to account for design effect and 10% loss to follow up as shown below is expected to be sufficient for the study.

- (i) Sample size formula for RCT considering simple random sampling:

$$2N = \frac{4(Z_{\alpha} + Z_{\beta})^2 \sigma^2}{\delta^2}$$

Where

2N is number of participants in two arms

$Z_{\alpha}$  is point on standard normal distribution corresponding to level of confidence of the study estimated to be 1.96 for 95% Confidence Interval

$Z_{\beta}$  is value corresponding to 85% power of the study =1.03

$\sigma$  is known mean DMFT from a previous study in Ndola, Zambia by Nasilele et al (2018)=1.34

$\delta$  is the expected clinically significant change in mean DMFT set at 20% =0.268

Based on assumptions and known values above the sample size for 2 arms is calculated as follow:

$$2N = \frac{4(1.96+1.03)^2 (1.34)^2}{(0.268)^2}$$

$$2N = 894.01 = 894$$

- (ii) Sample size considering cluster design, hence adjusting for design effect

$$n_c = n_1 [1 + (m - 1) \rho]$$

$$n_c = 894 [1 + (80 - 1) 0.01]$$

$$n_c = \text{estimated to be } 1600.26 = 1600$$

Where

$n_c$  = Number of pupils/participants in cluster per arm

$n_1$  = Individual number of participants (pupils) in an arm when considering random sampling

$\rho$  = Estimated intra-cluster correlation coefficient (ICC) to be 0.01

$m$  = Estimated cluster size in this study is 80 students in a class

- (iii) Sample size adjustment to consider loss to follow up assumed at 10%

$$n_c = 1600 + \{1600 \times (10/100)\} = 1760$$

$$\text{Final minimum sample size considered} = 1760$$

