#### **4.7. Randomization**

Allocation of clusters (secondary schools) into intervention and control groups will be done by stratified block randomization procedure whereby the district will be a stratifying unit and schools a blocking unit. Four randomly selected schools in the three districts will be listed in alphabetical order and assigned numbers 1 to 4. Computer random number generator will be used to randomly allocate 2 clusters in intervention and 2 in control groups in each district. The first two numbers generated will be allocated to intervention and the second two in control.

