## **4.9. Data collection procedures**

### **4.9.1. Data collection tools and indices**

Data will be collected using self-administered structured questionnaire and oral clinical examination. The questionnaire (Appendix 1) will be in English and will inquire on; demographic information of the participant's oral health knowledge and related behaviors and impact of oral diseases on daily performance of the adolescent. It will further inquire on parental/guardian socio-economic status using international wealth index (Smits and Steendijk, 2015). The students will understand the questions for the reason that they are fluent in English language.

Oral clinical examination will be done in a well illuminated classroom by two trained and calibrated dentists. Examination will be done using dental explorer aided by a mouth mirror and artificial light. The participants' will be lying on a desk and the examiner seated behind the participant's head. Every examiner will have one recorder who will be seated close to the examiner to ensure that the findings are recorded correctly.

Data collection will be done in four phases; baseline, every six months after institution of intervention that is; first follow up (6 months), second follow up (12 months), third follow up (18 months) and last follow up (24 months). The data collected for every adolescent will be paired and analyzed in pair. The principal investigator will assign a range of numbers for each school to be used as adolescent's identity number for baseline and all follow ups. School teachers will then be requested to create a list of names according to attendance register of that school and assign numbers to the individual participants. A copy of list of names and ID numbers will be kept by head teacher in case the teacher responsible for health is absent. Data for each variable will be entered and analyzed as set (baseline, 1st, 2nd, 3rd and 4th follow up).

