## Appendix 6- Analysis Plan by objectives

| No | Objective                                                                                                                                                                       | Analysis                                                                   | To be reported as                                              |
|----|---------------------------------------------------------------------------------------------------------------------------------------------------------------------------------|----------------------------------------------------------------------------|----------------------------------------------------------------|
| 1  | To determine prevalence and distribution of dental caries, periodontal conditions and oral impacts on daily performance among adolescents in Copperbelt Province, Zambia        | Frequency distribution, chi-square test, logistic regression               | Number and percentage, odds ratio with 95% confidence interval |
| 2  | To determine the association between dental caries and oral health related quality of life among adolescents in Copperbelt Province                                             | Frequency distribution, chi-square test, hierarchical logistic regression  | Number and percentage, odds ratio with 95% confidence interval |
| 3  | To assess the effects of a six months modified basic package of oral care intervention on knowledge and behaviors related to dental caries after 18 and 24 months of follow up. | Frequency distribution, chi-square test, generalized estimating estimation | Number and percentage, odds ratio with 95% confidence interval |
| 4  | To assess the effects of a six months modified basic package of oral care intervention on prevalence of dental caries after 6 and 12 months of follow up                        | Frequency distribution, chi-square test, generalized estimating estimation | Number and percentage, odds ratio with 95% confidence interval |
| 5  | To assess the effects of a six months modified basic package of oral care intervention on prevalence of oral impacts on daily performance after 18 and 24 months of follow up   | Frequency distribution, chi-square test, generalized estimating estimation | Number and percentage, odds ratio with 95% confidence interval |

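### Section 4.12 and Appendix 6 compare arms with pupil-level chi-square tests although schools are randomised, and the GEE is not stated to use school as its unit

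*Protocol*

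**What the plan says.** **Design.** Protocol section 4.7: "Allocation of clusters (secondary schools) into intervention and control groups will be done by stratified block randomization procedure", where "the district will be a stratifying unit and schools a blocking unit". Section 4.4 multiplies the simple-random-sampling size by 1 + (80 − 1) × 0.01 = 1.79, so the protocol itself treats pupils of one school as correlated.

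**Analysis.** Section 4.12 plans chi-square cross-tabulations and binary logistic regression. It adds that "cross tabulation for bivariate comparison of differences in intervention outcome variables by socio-demographics, study arms and oral health behaviors will be conducted". It then assigns the comparison of groups for effectiveness to generalized estimating equations, reported as odds ratios with 95% intervals. One threshold covers everything: "A statistical significance difference shall be assumed when" p ≤ 0.05.

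Appendix 6 gives the same methods for each of objectives 3, 4 and 5: "Frequency distribution, chi-square test, generalized estimating estimation". Nothing marks the chi-square test as descriptive. For objective 1 it lists chi-square and logistic regression, and for objective 2 chi-square and hierarchical logistic regression.

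The Summary names adjusted binary logistic regression together with GEE for differences between the groups at baseline and follow-up, without saying which method serves which comparison.

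**Dependence.** Section 4.9.1 says "The data collected for every adolescent will be paired and analyzed in pair". No section says that school is, or is not, the unit of the GEE.

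**The concern.** A Pearson chi-square test or an ordinary logistic regression on pupils assumes that every pupil contributes independent information. When whole schools are allocated, the difference between arms also carries school-to-school variation, which those methods leave out of the standard error. P-values then come out too small. The sample size calculation pays for clustering, but the listed tests do not use that allowance.

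Objectives 3 to 5 carry the effectiveness questions. With a chi-square p-value and a GEE p-value for the same comparison and one significance rule for both, a positive claim could rest on the invalid one. Objectives 1 and 2 raise a related point, because pupils are sampled by school (section 4.5).

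**Working it through.** **Inputs.** Section 4.4: z for alpha "estimated to be 1.96 for 95% Confidence Interval"; z for power "is value corresponding to 85% power of the study =1.03"; σ 1.34; δ 0.268; ICC 0.01; cluster size 80; 10% loss. Section 4.5: 18 schools of 90 to 100 pupils. Section 4.7: 4 schools in each of 3 districts = 12.

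**Step 1. The plan's own figure.** 4 × (1.96 + 1.03)² × 1.34² / 0.268² = 894.01. Then 894 × 1.79 = 1600.26, and 1600 × 1.10 = 1760. This reproduces exactly.

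**Step 2. A between-arm test that ignores school.** With DE = 1 + (m − 1) × ICC, the true two-sided error is 2 × [1 − Φ(1.96 / √DE)]. At ICC 0.01:

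| Setting | m | DE | True type I error | Multiple of 5% |
|---|---|---|---|---|
| Section 4.4 | 80 | 1.79 | 14.3% | 2.9 |
| Section 4.5, lower | 90 | 1.89 | 15.4% | 3.1 |
| Section 4.5, upper | 100 | 1.99 | 16.5% | 3.3 |
| 1600 pupils in 12 schools | 133.3 | 2.32 | 19.9% | 4.0 |
| 1760 pupils in 12 schools | 146.7 | 2.46 | 21.1% | 4.2 |

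**Step 3. Intervals from a model that ignores school.** The standard error is too small by √DE: √1.79 = 1.34 and √1.99 = 1.41.

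**Step 4. Sensitivity to the ICC** (assumed values, m = 80 to 100): ICC 0.002 gives 6.9 to 7.3%; 0.005 gives 9.7 to 10.9%; 0.02 gives 22 to 26%; 0.05 gives 38 to 42%.

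**Step 5. A GEE with school as subject and an uncorrected sandwich variance.** With k equal schools per arm the error is about P(|t with 2k − 2 df| > 1.96 × √((k − 1)/k)). For k = 9 this is 8.3%; for k = 6 it is 10.4%.

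**Step 6. Simulation check.** 20,000 null trials per setting, beta-binomial schools, ICC 0.01, assumed prevalence 40%, district strata ignored:

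| Schools × pupils | Pooled chi-square | School-level GEE, uncorrected | t-test on school proportions |
|---|---|---|---|
| 20 × 80 | 14.2% | 7.9% | 5.0% |
| 18 × 90 | 15.7% | 8.6% | 5.0% |
| 18 × 98 | 16.6% | 8.5% | 5.1% |
| 12 × 133 | 19.5% | 10.1% | 4.9% |
| 12 × 147 | 20.7% | 10.2% | 4.9% |

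The simulation agrees with the formulas. The school-level t-test holds the nominal level.

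These figures are for the arm comparison, where exposure is constant within a school. They do not carry over unchanged to objectives 1 and 2, where factors such as sex vary within schools.

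**The case against.** The strongest reply is that section 4.12 assigns effectiveness to the GEE, a method made for correlated data, and that its subject, working correlation, variance correction and covariates are details a statistical analysis plan may settle. That stands for the GEE: an unstated unit is not a wrong unit.

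A reader might go further and infer that school clustering is ignored throughout, taking the pairing sentence in section 4.9.1 as the definition of the GEE. The documents do not support this. The sentence belongs to data collection, next to the text on identity numbers, and does not mention the GEE. It follows that the two- to fourfold error rate cannot be attached to every effectiveness claim. It applies to the chi-square tests, to ordinary logistic regression, and to a GEE only if the pupil were its subject. The interval factor is limited further, because a chi-square test yields no interval. It concerns only ordinary logistic regression and a pupil-level GEE.

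Nor can objective 2 be described as ordinary logistic regression. Appendix 6 says hierarchical, which could mean a multilevel model or block entry of covariates. Baseline adjustment and the choice among small-sample methods are recommendations; leaving them out contradicts nothing.

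The reply does not rescue the chi-square tests. They are named for the effect objectives, with no cluster adjustment and no descriptive label, in a protocol whose own sample size assumes clustering.

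**Conclusion.** The point holds in this form: ordinary between-arm chi-square tests are planned in a school-randomised trial, the Summary adds binary logistic regression for group differences, and the GEE is not stated to account for school. At the protocol's ICC of 0.01 and 80 to 100 pupils per school, a test that ignores school runs at about 14 to 17% rather than 5%. If the 12 schools of section 4.7 hold the whole sample, the figure is about 20 to 21%. Intervals from a model that ignores school would be too narrow by about 1.34 to 1.41.

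Naming school as the GEE subject removes most of the excess but not all of it: about 8 to 9% remains with 18 schools and about 10% with 12, unless the variance or reference distribution is corrected.

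All figures assume equal school sizes, and the simulated ones also assume 40% prevalence and ignore district strata. The size depends strongly on the ICC, for which the protocol gives one estimate. The discrepancy between 12 and 18 schools is a separate matter, but it must be resolved before the degrees of freedom can be set.

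**What to change.** Amend section 4.12, Appendix 6 and the Summary:

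1. Remove the chi-square and ordinary logistic tests from comparisons between arms, keeping the cross-tabulation as description, or replace them with cluster-adjusted versions.
2. Name school as the independence unit of the GEE, with each pupil's visits nested in it.
3. Use a small-sample corrected variance with a t reference, or a district-stratified analysis of school-level summaries. Either way, include district. Adjusting for the pupil's baseline value is advisable but optional.
4. Account for sampling by school in the objective 1 tests and the objective 2 chi-square, and state what hierarchical means for objective 2.

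No new data are needed. The cost is wider intervals and a little more analysis work. With district in the model the degrees of freedom are schools minus 4, so the critical value rises from 1.96 to 2.145 with 18 schools (2.145 / 1.96 = 1.09) or 2.306 with 12 (2.306 / 1.96 = 1.18). Whether the chosen correction is available in SPSS version 23, which section 4.12 names, should be checked. An analysis of school-level summaries needs only standard routines.
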